**Methods:**

This study is a prospective, superiority, multicenter, non-masked, randomized controlled trial that investigates the outcome and hospitalization medical expense of SINTNP compared to TNP for PE. A total of 320 eligible patients according to sample size calculation by retrospective data will be randomly assigned to the SINTNP group or the TNP group at a 1:1 ratio using stratified blocked randomization and the zone length was set as four. Patients aged between 3 and 18 years old for the first surgery and without combination of complex anomalies such as Marfan syndrome and congenital heart disease will be considered for the study. The co-primary endpoint is thoracic related complications and medical expense during hospitalization. Thoracic related complications were defined as pneumothorax, pleural effusion, pneumonia and incision infection. The secondary endpoints include surgery duration and length of hospital stay.

The registration number for this study protocol is ChiCTR230073081 (Chinese Clinical Trial Registry, A Primary Registry of International Clinical Trial Registry Platform, World Health Organization).

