## Background

1.

Pectus excavatum is the most common anterior chest wall deformity in children (1). The Nuss procedure is the appropriate method for treating pectus excavatum in the majority of patients (2). Nuss initially reported a minimally invasive technique using bilateral incisions without the assistance of thoracoscopy (3). Subsequently, in a survey of members of the American Association of Pediatric Surgeons, 61% of members used thoracoscopic assistance during Nuss surgery to reduce the risk of cardiac or pulmonary injury (4). [name] himself also emphasized that thoracoscopic assistance has been highly recommended since 1998 (5). Hence, the majority of surgeons tend to use thoracoscopic assistance in Nuss surgery (6), especially in adults (7).

However, the situation in the field of children may be different. Trained surgeons can safely pass bar through the space behind the sternum without relying on thoracoscopy in children because children's sternum is softer and more malleable. Only 49% of members of the Chinese Association of Thoracic Surgeons consider thoracoscopy to be a necessary method to avoid heart injury during the Nuss procedure (8). Additionally, if unilateral fixation can ensure the stability of the steel plate, then bilateral incisions are not necessary. Our center has been attempting modified single incision non-thoracoscopic Nuss procedure (SINTNP) since 2017 and has completed over 400 such surgeries to date, without any cardiac injury. The specific method of surgery can be found in our previous report (9, 10).

We speculate that modified single incision non-thoracoscopic Nuss procedure can reduce hospitalization costs, the proportion of thoracic-related complications, and the length of hospital stay in patients. Therefore, we conducted this multicenter randomized controlled trial to confirm the clinical value of SINTNP for pediatric patients compared with the thoracoscopic Nuss procedure (TNP) with bilateral incision.

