#### Primary objectives

2.1.1.

The coprimary objectives of the study are to assess differences in thoracic-related complications and medical expenses during hospitalization of PE patients undergoing SINTNP or TNP.

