### Sample size and recruitment

2.6.

Medical expense during hospitalization is the primary outcome indicator of this study because it can objectively evaluate the financial burden of the patient's family. Based on our retrospective research data on surgeries over the past three years, the average cost of the TNP group was 30,250 RMB, while the average cost of the SINTNP group was 28,157 RMB. The standard deviation will be set as 2,000, and the superiority margin will be set as 1,500. The sample size will be calculated to require at least 141 children in each group.

The proportion of thoracic-related complications was approximately 9.6% in SINTNP and 13.6% in nonthoracoscopic-assisted Nuss surgery with double incision. The sample size calculation requires over 3,000 people per group according to the proportion of thoracic-related complications, and currently, we are unable to recruit so many patients. We will truthfully describe this recruitment-related limitation in the officially published article. Considering a 10% to 15% withdrawal and dropout rate, each group will ultimately include 160 children.

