### Statistical methods

2.11.

Continuous data will be presented as the means with standard deviations (SDs) or medians with interquartile ranges (IQRs). The Kolmogorov–Smirnov test will be used to evaluate normality. Continuous data will be compared between the two groups by unpaired t test (normal distribution) or the Mann‒Whitney *U*-test (nonnormal distribution). A chi-square test will be used to compare categorical variables between two groups. Pre-protocol analysis (PP) will be performed with data of participants finishing the whole study and intention to treat analysis (ITT) will be used in full analysis set. Inter group analysis across centers were performed to evaluate the influence of bias and the reliability of the overall study.

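### The protocol contradicts itself on whether expense alone or expense and complications together decide the trial, and the likeliest result (expense alone significant) has no agreed verdict

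*Protocol article*

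**What the plan says.** The abstract states: "The co-primary endpoint is thoracic related complications and medical expense during hospitalization". Section 2.1.1 repeats this: "The coprimary objectives of the study are to assess differences in thoracic-related complications and medical expenses during hospitalization". Section 2.5.1 lists the same two outcomes under its co-primary heading.

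Section 2.6 reads differently: "Medical expense during hospitalization is the primary outcome indicator of this study". It bases the sample size on expense only: "the average cost of the TNP group was 30,250 RMB, while the average cost of the SINTNP group was 28,157 RMB", then "The standard deviation will be set as 2,000, and the superiority margin will be set as 1,500", and concludes "The sample size will be calculated to require at least 141 children in each group". It adds that a calculation on complications would need more than 3,000 per group, which cannot be recruited, and promises to report this as a limitation. Complications nevertheless stay co-primary elsewhere.

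Section 2.11 assigns a t test or Mann–Whitney test to continuous data and a chi-square test to categorical data, and plans two analysis sets ("Pre-protocol analysis (PP) will be performed with data of participants finishing the whole study and intention to treat analysis (ITT) will be used in full"). The article gives no significance level.

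**The concern.** With two endpoints called co-primary, a reader must know whether one success is enough or both are needed. The sections shown point in different directions. Section 2.6 implies that expense decides. The abstract and sections 2.1.1 and 2.5.1 give complications equal rank, and "co-primary" is often understood to mean that both must succeed.

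This would not matter if the two endpoints were likely to agree. They are not: the trial is sized for expense and, by its own admission, far too small for complications. A split result is therefore the expected one, and its verdict could be chosen after the data are seen. The same freedom applies between the per-protocol and full analysis sets, because section 2.4 removes children with plate allergy or poor wound healing from the first and keeps them in the second.

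**Working it through.** **Inputs from section 2.6.** Mean cost 30,250 (TNP) and 28,157 (SINTNP) RMB, so the difference is 2,093. The margin is 1,500, so the excess over the margin is 593. SD 2,000. Complications 9.6% with SINTNP. The comparator figure of 13.6% is for double-incision *non-thoracoscopic* surgery and is used here only as a stand-in for TNP. n = 141 per group, or 160 with the dropout allowance.

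**Step 1: reproduce 141.** n = 2 × SD² × (z₁₋α + z₁₋β)² / 593².
- One-sided 5%, 80% power: 2 × 2,000² × (1.645 + 0.842)² / 593² = 140.7, so 141. Exact match.
- One-sided 2.5%, 80% power: 178.6, so 179.

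The stated size thus corresponds to a full one-sided 5% on expense, with nothing reserved for a second primary test. This is an inference, since the article states no alpha.

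**Step 2: power of each endpoint.**
- Expense against the margin: z = 593 / (2,000 × √(2/n)) = 2.49 at n = 141 and 2.65 at n = 160. Power at one-sided 5% is 80.1% and 84.3%.
- Complications: z = 0.04 / √((0.096 × 0.904 + 0.136 × 0.864)/n) = 1.05 and 1.12. Power is 18.2% and 20.0% at two-sided 5%, or 27.6% and 30.0% at one-sided 5%.

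**Step 3: result patterns**, multiplying the powers as if the endpoints were independent, with expense at one-sided 5%. Each cell gives n = 141, then n = 160.

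| Pattern | Complications two-sided 5% | Complications one-sided 5% |
|---|---|---|
| Expense only | 65.5%, 67.4% | 58.0%, 59.0% |
| Both | 14.5%, 16.9% | 22.1%, 25.3% |
| Complications only | 3.6%, 3.1% | 5.5%, 4.7% |
| Neither | 16.3%, 12.6% | 14.4%, 11.0% |

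Expense alone is the single most likely pattern in every column. If expense were tested by a plain t test without the margin (section 2.11 does not mention the margin), its power would be practically 100% and the expense-only share would be 80–82%.

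**Step 4: false-positive rate if either endpoint suffices**, each at one-sided 5%.
- Independent endpoints: 1 − 0.95² = 9.75%.
- Correlated test statistics (bivariate normal): 9.3% at correlation 0.3, 8.8% at 0.5, 7.5% at 0.8.

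For expense, these figures apply at a true saving of exactly 1,500 RMB, the boundary of the margin hypothesis. At a true saving of zero and n = 141, the statistic is centred at −1,500 / (2,000 × √(2/141)) = −6.3, and the margin test practically never rejects.

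**Step 5: false-positive rate if both must succeed.** It is at most 5%, so there is no inflation. The price is the joint power in the "Both" row.

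**Step 6: two analysis sets.** In a simulation with 160 per arm, 10–15% random exclusion from the per-protocol set and endpoint correlation 0 to 0.6, accepting a win on either endpoint in either set gave about 11–13% at one-sided 5%. That is some 2–3 points above one set alone, because the sets largely overlap.

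**The case against.** The strongest reply is that this is a condensed article. A testing order, an alpha split and the choice of primary set commonly sit in a statistical analysis plan, which may exist and is not shown. That stands: their bare absence is not counted here as an error. What an unseen plan cannot do is make section 2.6 agree with the abstract and sections 2.1.1 and 2.5.1 on what is primary.

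Several stronger readings are tempting and are not supported:
- *Each endpoint is tested at full alpha.* The article states no alpha. The value for expense is inferred from 141, and nothing fixes one for complications.
- *The false-positive rate doubles.* That follows only if either endpoint suffices. It also needs one-sided 5% tests: at two-sided 5%, a false claim in favour of SINTNP arises 2.5% of the time per test.
- *Two endpoints in two sets make four free primary tests.* The overlap of the sets limits the addition to a few points.
- *Length of stay is a further primary claim.* The Background speculates that SINTNP "can reduce hospitalization costs, the proportion of thoracic-related complications, and the length of hospital stay in patients", but the abstract and sections 2.1.2 and 2.5.2 label length of stay secondary.

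It is also fair to object that the complication figures are soft. The 13.6% is not a TNP rate, and 9.6% against 13.6% needs about 1,005 per group (two-sided 5%, 80% power), not over 3,000. The planned effect is therefore unclear. A smaller effect would make a split result more likely, not less.

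**Conclusion.** The contradiction holds and bears on the result the trial is most likely to produce. Expense alone is significant in about 58–67% of trials, and the sections disagree on whether that is a success. If either endpoint counted at an unadjusted one-sided 5%, the false-positive rate would be about 7.5–9.8% (correlation 0.8 to 0, with the true saving at the margin). If both were required, error would not be inflated, but joint power would be about 15–17%, or 22–25% with complications one-sided.

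These sizes rest on the alpha implied by 141, on independent endpoints for the pattern and joint-power figures, and on 13.6% as a stand-in for TNP. The disagreement between the sections rests on none of these.

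**What to change.** Align the abstract and sections 2.1.1, 2.5.1, 2.6 and 2.11 on one order of testing:
1. Medical expense is the deciding primary endpoint, tested in the intention-to-treat/full analysis set against the 1,500 RMB margin at one-sided 5%, the level implied by 141. State that level.
2. Thoracic-related complications are tested at the same level only if expense succeeds.
3. Length of stay and surgery duration are reported as secondary.
4. The per-protocol analysis is labelled a sensitivity analysis that cannot overturn the intention-to-treat result.

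Section 2.2 announces noninferiority tests, whereas the abstract and section 2.6 speak of superiority. This is a separate inconsistency, best settled in the same edit.

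The cost is wording: no extra children, and no loss of power for expense. A difference in complications without one in expense, about 3–5.5% of trials under the assumptions above, could no longer be claimed as confirmatory. Choosing expense as the deciding endpoint is the sponsor's decision, but it is the choice that matches the trial's own sizing. The Results section says the study had not started, while section 2.13 forbids any modification after publication, so the correction must be openly documented before the trial starts.

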### Monitoring

2.12.

A Data Monitoring Committee (DMC) will be established to ensure the wellbeing of study participants. The DMC will periodically review study progress and outcomes as well as reports of unexpected serious adverse events (SAEs). The DMC will, if appropriate, make recommendations to the Trial Steering Committee (TSC) regarding continuance of the study or modification of the study protocol.

When any SAEs occur, the researcher will immediately report it to the committee and be authorized by the committee to terminate the study. SAEs include (1) incision infection; (2) bar exposure; (3) bar displacement; (4) VAS score higher than 8 after using analgesic; and (5) obvious bar allergy. All adverse events will be truthfully recorded in the CRF form and reported in the final research results.

Independent investigators from the Ethics Committee of Children's Hospital of Chongqing Medical University will review the standardization of the study every two weeks and randomly observe the process of patient recruitment, doctor‒patient communication, surgical implementation, and outcome evaluation by researchers. Investigators will be independent to researchers and sponsors and will not sign their names in the final manuscript. We will thank them for their contributions to the research in the acknowledgment section.

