#### Coprimary outcomes

2.5.1.

Thoracic-related complications include pleural effusion, pneumothorax, and pneumonia diagnosed on chest radiograph.

Medical expenses during hospitalization are the total expenses recorded in the hospitalization electronic system, all of which are the original expenses before insurance reimbursement and are denominated in RMB.

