### Ethics and dissemination

2.13.

This study was approved by the Ethics Committee of Children's Hospital of Chongqing Medical University (approval number: 2022-325) and was registered in the Chinese Clinical Trail registry. The version number of this protocol is 2023-06, and the version is confirmed on April 8, 2023. The protocol may be slightly modified during the submission stage based on the comments of the reviewers and editors. After the publication of the research protocol, any form of modification of the research protocol is prohibited in this study. All of the children's guardians signed a consent form confirming participation in the study and authorizing the authors to collect the clinical data and publish potential research findings. This study will not conduct additional collection of biological samples from patients.

We will not record the name and contact information of the patient but instead use numerical numbers. Patient personal information will not be disclosed to any institution or individual. There were no financial or other competing interests for principal investigators for the overall trial and each study site.

The research committee board composed of HL, LZ, YX and LX has access to the final trial dataset. After the final research report is published, we will fully disclose the final trial dataset. Both surgical methods used in this study have been proven to be safe and reliable and are not expected to pose additional risks to patients. If the patient in this study suffers serious complications, we will provide all necessary assistance and compensation according to regulations.

Our final data will be attached to the final article for publication. Once the article is published, we will inform trial results to participants, health care professionals, the public, and other relevant groups via email.

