## Discussion

4.

Heart injury is the most dangerous complication of pectus excavatum, so all surgeons will do their best to avoid it (12). A practical and feasible approach is to observe through thoracoscopy (13). Through thoracoscopy, the surgeon can clearly observe the process of tunnel establishment and bar passing through the sternum. Aberrant vessels detected in the mediastinal pleura could be evaded under direct visualization during mediastinal dissection with thoracoscopy (14). Additionally, it is traditionally believed that the bar needs to be fixed bilaterally to avoid displacement, so thoracoscopy usually does not add additional incisions. Thoracoscopic assistance is necessary in adults, especially in patients with recurrence, history of previous thoracic procedure or double-bar insertion (7, 15).

However, for children who undergo their first surgery and only need to use one bar in preoperative evaluation, thoracoscopic assistance may be redundant. Children's sternum is relatively soft and malleable, and separation behind the sternum is usually safe. Especially considering the recent use of single-incision Nuss surgery, thoracoscopic assistance is difficult and may not be necessary (10). We are worried that the thoracoscope entering the pleural cavity will cause additional pulmonary complications. Excessive pain and prolonged hospital stay time may reduce the quality of life of the patient and parents after surgery, while also increasing the workload and burden of clinical doctors. We hope to reduce the surgical costs and postoperative hospital stay of the patient. In a relatively underdeveloped region such as western China, a considerable proportion of patients still struggle to bear the cost of surgery (16). Therefore, we must strive to reduce their burden.

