In the study, we only compare SINTNP to TNP and do not focus on the comparison between double incision non-thoracoscopic Nuss Procedure (DINTNP) to TNP. This is mainly due to two reasons. Firstly, because TNP requires two incisions, if we also use two incisions in non-thoracoscopy assisted Nuss surgery, then we do not utilize the advantages of non-thoracoscopy assisted surgery. Theoretically, DINTNP takes longer and has more injuries compared with single incision. The other reason is that our previous research has confirmed that the SINTNP will not increase the probability of postoperative bar displacement compared with the DINTNP. SINTNP is safe and reliable. Therefore, the current research setup is more in line with clinical scenarios.

Hence, we conducted this multicenter randomized controlled study. We believe that the results of this study are generalizable to other populations or healthcare settings. The learning curve of Nuss procedure is not long. Most thoracic surgeons can master this technique skillfully after a 10-procedure proctoring period (17). Non Thoracoscopy assisted single incision surgery has been carried out in many institutions. In addition, perioperative evaluation and nursing methods are also very common. The vast majority of institutions can perform preoperative CT, lung function, and echocardiography on children. Previous literature did not report significant cross regional or racial differences in the prognosis of Nuss surgery. Therefore, we believe that the results study can be widely generalized.

It is worth noting that although all researchers have undergone standardized training and each center's research will strictly follow the protocol. The potential bias in patient recruitment, protocol implementation, and data collection in multicenter studies cannot be completely avoided. We would like to confirm that for children with pectus excavatum who undergo their first surgery and need to use only one bar, the single-incision nonthoracoscopic Nuss procedure is sufficient. Other methods for ensuring safety, such as thoracoscopy or bilateral incision, are unnecessary.

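### The ban on protocol changes contradicts the monitoring plan, the termination clause is unclear, and the hoped-for safety conclusion rests on an injury the trial neither names nor can closely bound

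*Protocol article*

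**What the plan says.** Four places in the protocol article bear on this.

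- **Changing the protocol.** Under section 2.12 (Monitoring) the DMC may "make recommendations to the Trial Steering Committee (TSC) regarding continuance of the study or modification of the study protocol". Section 2.13 (Ethics and dissemination) says that, once the protocol is published, "any form of modification of the research protocol is prohibited in this study".
- **Terminating.** Section 2.12 continues: "When any SAEs occur, the researcher will immediately report it to the committee and be authorized by the committee to terminate the study". It then lists five events, beginning "SAEs include (1) incision infection; (2) bar exposure; (3) bar displacement" and going on to a high pain score despite analgesia and obvious bar allergy. Section 2.4 (Interventions) says that a child with a clear tendency to plate allergy, or with poor wound healing such as suppuration, leaves the study.
- **Heart injury.** The Discussion states: "Heart injury is the most dangerous complication of pectus excavatum, so all surgeons will do their best to avoid it". The Abstract and Background give avoidance of cardiac injury as the reason surgeons use thoracoscopy. Section 2.5.1 defines the complication outcome thus: "Thoracic-related complications include pleural effusion, pneumothorax, and pneumonia diagnosed on chest radiograph". The Abstract has "Thoracic related complications were defined as pneumothorax, pleural effusion, pneumonia and incision infection". The secondary outcomes are surgery duration and length of stay.
- **Conclusion sought.** The end of the Discussion expresses the hope of confirming that SINTNP is sufficient for children having a first operation with one bar, and adds: "Other methods for ensuring safety, such as thoracoscopy or bilateral incision, are unnecessary".

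**The concern.** The first two items are conflicts within the monitoring plan. If the DMC saw a safety signal and recommended a change, section 2.13 read as written would forbid it. If a listed event occurred, a site could not tell from the text whether one child or the trial is affected, or which body decides.

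The other two concern what the trial can say about safety. The experimental arm omits the step that, by the article's account, exists to prevent heart injury. A statement that this step is unnecessary for safety is a statement about that injury. The injury is not a named endpoint, and the sample size comes from expense. A trial with no heart injuries could then be read as having shown something it had little ability to show.

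**Working it through.** **1. Modification.** Section 2.12 provides a route by which the DMC advises the TSC to modify the protocol. Section 2.13 prohibits modification of any form after publication and makes no exception for safety. A DMC recommendation to modify could therefore be made but not enacted.

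**2. Termination.** The article mentions four bodies to which the unnamed committee could refer: the DMC, the TSC, the research committee board and the Ethics Committee. Bar allergy appears in both section 2.4 and the SAE list. Incision suppuration (2.4) overlaps with incision infection (2.12). Section 2.4 attaches withdrawal of the child to these events; section 2.12 attaches termination of the study, with its scope undefined.

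**3. Where heart injury could be named.** It is absent from the Abstract's definition of the complication outcome, sections 2.1.1, 2.1.2, 2.5.1 and 2.5.2, Table 2, and the five listed SAEs. The cardiac function entry in Table 2 is defined only as mitral valve prolapse or arrhythmia.

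**4. What fixes the sample size.** Section 2.6 gives mean expenses of 30,250 and 28,157 RMB, SD 2,000 and margin 1,500.

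- Difference beyond the margin: 30,250 − 28,157 − 1,500 = 593.
- n per group = 2 × (1.645 + 0.842)² × 2,000² / 593² ≈ 140.7, rounded up to 141.

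This reproduces the stated 141 with one-sided alpha 0.05 and 80% power. Neither is stated, so both are assumptions. Two-sided 0.05 with 80% power would give 179. The trial is thus sized on expense; allowance for dropout brings each group to 160.

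**5. What zero heart injuries would show.** With no events in n children, the exact binomial upper 95% limit is 1 − 0.025^(1/n) two-sided, or 1 − 0.05^(1/n) one-sided.

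| Children, no events | Two-sided limit | One-sided limit |
|---|---|---|
| 160 (planned SINTNP arm) | 2.28% | 1.85% |
| 141 (arm after dropout) | 2.58% | 2.10% |
| 400 (series cited in the Background) | 0.92% | 0.75% |

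A fall from 160 to 141 is 19/160 = 11.9%, inside the 10% to 15% that section 2.6 expects. The Background reports more than 400 operations; 400 is used here, so the third row is slightly conservative.

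**6. Chance of seeing any event in 160.** The article gives no heart injury rate. For assumed true rates of 0.1%, 0.2%, 0.5% and 1%, 1 − (1 − rate)^160 gives 15%, 27%, 55% and 80%. Even at 1%, the arm would show no injury about one time in five.

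**The case against.** **Heart injury would not go unseen.** The SAE list is introduced by a word that need not make it exhaustive, section 2.12 has every adverse event entered in the CRF and reported, and the DMC reviews unexpected SAEs. This stands. A reader might infer that a cardiac injury could occur and never be reported; the document does not support that. What remains is that the injury is neither a named reporting trigger nor an outcome set out for comparison by arm.

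**Termination needs a committee's authorization.** This also stands. A reader might infer that a researcher can end the trial without independent review. The text does not say so: a committee must authorize, and it may be the DMC or TSC introduced just before. Nor does it say that any single SAE stops the trial automatically. The phrase may mean ending one child's participation, which would fit section 2.4. No event rate is given from which a chance of stopping could be computed. The fault is ambiguity.

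**The conclusion is a hope.** It appears in the Discussion, is limited to first-surgery, single-bar children, and is not among the objectives. Calling it a planned analysis conclusion would be too strong. It is still the safety message that the article says it wants to confirm.

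**No trial of this size could exclude a rare injury, and naming it will not change that.** True. That is an argument for narrowing the conclusion. The ban on changes may be meant to prevent outcome switching, a sound aim, but as worded it also blocks safety amendments.

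**Conclusion.** The point holds in four parts of unequal strength.

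- The clash between sections 2.12 and 2.13 on modification is firm and needs no assumption.
- The termination wording is unclear about the deciding body and the scope, and sits awkwardly with section 2.4. The passages must be reconciled; no stopping rule is implied here.
- Heart injury is missing as a named outcome and listed SAE. It would probably be captured by general adverse event recording, so this is a weakness in definition and reporting.
- The safety conclusion hoped for is beyond the trial's reach. No injury among 160 would leave up to 2.28% (two-sided) compatible with the data, about two and a half times the 0.92% from the existing series (2.28 / 0.92 = 2.5).

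The limits are exact. They assume that all 160 have SINTNP and are assessed for the injury; losses before assessment widen them. The comparison with the 400 cases concerns only the precision of a single-arm rate: that series comes from one centre and has no concurrent control, whereas the trial adds other centres and a randomized comparator.

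**What to change.** 1. In section 2.13, replace the ban with a dated, ethics-approved amendment record, so that DMC recommendations can be enacted and changes remain traceable.
2. Reconcile sections 2.4 and 2.12: name the committee, and say whether termination concerns one child or the trial and how it relates to the DMC and TSC route.
3. Add heart, pericardial and great-vessel injury to the SAE list, and report it by arm with exact confidence limits.
4. In the Discussion, confine the intended conclusion to expense and in-hospital thoracic complications, keeping the recruitment limitation that section 2.6 already admits for the latter, and drop the statement that thoracoscopy is unnecessary for safety.

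The cost is small: wording in sections 2.4, 2.12, 2.13 and the Discussion, and a named entry for events that are to be recorded anyway. The article says that the formal study has not started. The sample size and primary analysis do not change; the price is a more modest conclusion. Because section 2.13 itself forbids changes after publication, item 1 has to be settled first, with the ethics committee.
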